##### Parental Sensitivity and Parent-Child Reciprocity

Parental sensitivity and parent-child reciprocity were assessed by direct observation of the caregiver and child sharing a book. The interaction was recorded on video and coded by independent assessors blinded to the group allocation using a coding system developed by LM, adapted for the book-sharing context. While specific modes of expressing sensitivity and reciprocity can vary between cultures [38,39], the core features are common across different populations, that is, supportive and warm responsiveness to infant cues and mutually positive active engagement. This coding system has been used previously in DBS studies, including the investigation of book-sharing impact in LMICs and middle-income settings in South Africa, Lesotho, Colombia, and Brazil. Notably, in one South African study, sensitivity and reciprocity were found to mediate the impact of the intervention on the development of child language and attention [21].

#### Secondary Outcomes

##### Child Attention

The Early Childhood Vigilance Task (ECVT) was used to assess child attention [40]. ECVT is a computer-based tool during which the child is shown a 7-minute-long cartoon. The child’s sustained attention is indexed by the number of seconds the child attends to the screen during the 7-minute period. The child was videotaped during the assessment, and the recording was subsequently independently scored. ECVT has been previously used in DBS studies [21,22].

##### Child Behavior

Child behavior was assessed using the full version of the Strengths and Difficulties Questionnaire [41], with aggregated scores obtained for the following scales: emotional symptoms, conduct problems, hyperactivity and inattention, relationship problems, and prosocial behavior as well as for a total score indexing total level of behavioral disturbance. The child’s prosocial behavior was further assessed during a help task [21,42]. In this direct assessment, the data collector creates a situation in which the child is encouraged to express a “helping behavior,” that is, to offer help in finding the item the data collector pretends to have lost.

##### Parenting

The frequency of caregivers joining the children in sharing a book at home and in other child games was assessed using diaries distributed to all caregivers in all groups. Caregivers were provided with an easy-to-fill-out diary for the 8-week intensive intervention period. Every day, caregivers circled pictograms of the child’s activities and the person or people who joined the child in that activity. Diaries were collected after the intensive intervention period.

To assess caregivers’ general parenting practices, 3 dimensions from the self-report short version of the Parenting Styles and Dimensions Questionnaire [43] were administered: the connection dimension to index the occurrence of warm and supportive behaviors, the physical coercion dimension to index the extent to which caregivers apply physical punishments, and the verbal hostility dimension to index the presence of harsh verbal behavior.

In total, 13 statements from the Tool to Measure Parenting Self-Efficacy questionnaire [44] were used to assess parenting efficacy concerning emotion and affection, play and enjoyment, empathy and understanding, control, discipline and setting boundaries, self-acceptance, and learning and knowledge.

##### Parental Stress

The Parental Stress Scale was administered to assess the level of parenting-related stress [45].

#### Exploratory Outcomes (Child Health)

To assess child health, caregivers reported whether the child experienced diarrhea in the past 2 weeks. In addition, children’s height and weight were measured to check their nutritional status (stunting, wasting, and underweight).

#### Potential Moderators

##### Sex of the Child

We examined the potential difference between the effects of the intervention on girls and boys.

##### Socioeconomic Situation of Families

We examined the potential difference in the intervention’s effects on children living in families of varying socioeconomic statuses using the asset index [46,47] as an indicator of socioeconomic status. The indicators recorded are defined based on the same taxonomy used, for example, in the Demographic and Health Surveys [48]. Following the procedures of Němečková et al [49], the individual items are weighted during aggregation using weights generated by the multiple correspondence analysis method, and the results are linearly rescaled to a 0 to 100 scale.

##### Cognitive Abilities of Caregivers

The shortened version of the Vienna Matrices Test [50] was administered to measure the cognitive abilities of caregivers.

### Fidelity Testing

Consistent delivery of both the DBS and PA programs was tracked with an 18-item implementation fidelity checklist. In total, 11 items assessed the substantive content of each session, for example, whether the facilitator explained key concepts clearly and gave accurate, supportive feedback during mothers’ practice, whereas 7 items captured organizational logistics and caregiver-oriented factors (eg, punctual arrival of facilitators and mothers, maternal attentiveness during the theoretical segment, distribution of porridge to children at the start of the session, and the babysitter’s behavior).

Each checklist item was transformed to a 0% to 100% scale; the mean of the 11 content items formed the content fidelity subscore, and the mean of the 7 organizational items formed the procedural fidelity subscore. A session was deemed adequate only when both subscores were ≥75%. Facilitators whose scores fell below this threshold received targeted supervisory feedback before the next block of sessions. Fidelity distributions will be summarized descriptively in trial reports.

An independent rater conducted live, in-person observations of 2 sessions per facilitator, with a minimum interval of 3 weeks between visits. Sessions were not audio or video recorded. Fidelity scores will be used solely to define the per-protocol analytic sample (dyads taught by facilitators whose average content and procedural fidelity across the 2 observed sessions are each ≥75%). Because the checklist serves primarily as a quality-assurance gate, fidelity will otherwise be summarized descriptively and will not be modeled as an explanatory variable.

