### Intervention

#### The Index Intervention Group (DBS)

The index intervention was a DBS program consisting of 8 weekly educational sessions for groups of 3 to 8 female caregivers, each lasting 90 minutes [15,20,22]. This stage of the intervention is called the intensive intervention phase. The content of weekly sessions was based on the Mikhulu Trust book-sharing program for children aged 15 to 30 months and the Mikhulu Trust book-sharing program for children aged 30 to 45 months, developed by LM and [name]. These programs have been shown to benefit parenting and child development [20-22]. The program for caregivers of children aged between 30 and 45 months is described in Table 1.

**Table 1 table1:** Summary of index intervention group sessions for caregivers of children aged between 30 and 45 months^a^.

Session number	Name of the session	Description of the session
1	Introduction to book sharing	Introducing basic dialogic book-sharing skills—following the child’s lead, using a lively voice, and setting up book-sharing routines
2	Pointing and naming	Basic dialogic book-sharing skills—pointing and naming, repeating and elaborating on things that interest the child, and finding opportunities for praise
3	Naming and linking	Asking “where, who, and what” questions, linking book content to the child’s own experience, and finding opportunities to use actions (eg, hugging and eating)
4	Talking about feelings	Helping the child understand the meaning of basic emotion terms—happy, sad, angry, and scared—and discussing why book characters feel the way they do, using facial expression and tone of voice to convey a character’s feelings, and linking feelings in the book to the child’s experience
5	Talking about intentions	Discussing why characters feel the way they do, asking what characters think and intend, and encouraging the child to be curious about what will come next in the story
6	Talking about perspectives	Helping the child understand that different people can see things differently, know different things, and feel differently about things
7	Summary	Reviews of key principles from sessions 1 to 6.
8	Graduation event	Certificates of completion presented to participants along with summary take-home cards and selected books from sessions 1 to 6; a group discussion about how to remain motivated about book sharing and how to access children’s books

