### Data Analysis

#### Statistical Analysis Plan

All data will be analyzed by an independent statistician using R (R Foundation for Statistical Computing) or Stata (StataCorp LLC). Fidelity will first be described with standard descriptive statistics. Hypothesis tests will be 2-sided with α of .05, and effect-size statistics will be reported to indicate the magnitude of any intervention effects.

Outcomes are classified a priori as primary, secondary, or exploratory. For the primary outcomes, we will use the Holm-Bonferroni method to adjust *P* values. Secondary and exploratory outcomes will be interpreted as hypothesis generating; the Benjamini-Hochberg procedure will be applied for their significance evaluation.

The primary and secondary outcome analyses will follow the intention-to-treat principle.

Linear mixed models or, where appropriate, analyses of covariance will evaluate intervention effects at both the intensive and extensive postintervention phases, always adjusting for baseline outcome scores. Because participants are clustered, a random effect will be included, and fixed-effect estimates will be compared with intercluster variability. Before modeling, every numerical predictor will be mean centered and standardized (*z* scores); interaction terms will be created as products of these centered variables. Candidate covariates and moderators (child age, dwelling place, child sex, socioeconomic situation, and parental cognitive abilities as indexed by education) will be retained only if they are significant or if removing them markedly alters other parameter estimates.

Although the intention-to-treat approach is the primary approach, a complementary per-protocol analysis will be performed to clarify whether any lack of impact arises from deficiencies in the intervention itself or from participants’ incomplete exposure to it.

Multicollinearity among predictors will be assessed using variance inflation factors, with appropriate mitigation strategies applied where necessary.

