#### Mediator and Moderator Analyses

Mediator analysis will discern whether improvement in caregiver sensitivity mediates intervention effects on child outcomes. In addition, we will investigate whether improvements in parental sensitivity mediate advancements in reductions of parental stress. Mediation analyses will be conducted using the product-of-coefficients approach (a series of path models within the mixed-effects framework). CIs will be obtained using bootstrapping.

To assess moderation, interaction terms between the intervention and possible moderators will be included in the model. Subsequently, the significance of the interaction will be tested. In moderator analyses, we will also conduct a subgroup investigation to identify variations in the differential effectiveness of the intervention across subgroups. Subgroup analyses will be conducted with respect to the number of sessions attended, child sex, living standard, and the cognitive abilities of the caregiver.

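### The per-protocol set is defined by facilitator fidelity, so it tests delivery quality and cannot show whether incomplete participant exposure explains a null result

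*Protocol article*

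**What the plan says.** All references are to the protocol article.

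- **Purpose** (Statistical Analysis Plan). Intention-to-treat is primary. A complementary per-protocol analysis is added "to clarify whether any lack of impact arises from deficiencies in the intervention itself or from participants’ incomplete exposure to it".
- **Definition** (Fidelity Testing). "Fidelity scores will be used solely to define the per-protocol analytic sample", and that sample is given in a bracket as "dyads taught by facilitators whose average content and procedural fidelity across the 2 observed sessions are each ≥75" per cent. The measurement behind it is described in the same section: "An independent rater conducted live, in-person observations of 2 sessions per facilitator, with a minimum interval of 3 weeks between visits".
- **Content of the score** (Fidelity Testing). There are 11 content items and 7 organisational items. Some of the 7 concern caregivers, for example "punctual arrival of facilitators and mothers, maternal attentiveness during the theoretical segment", but they are averaged into the score of the observed session.
- **Intended exposure** (The Index Intervention Group). "The index intervention was a DBS program consisting of 8 weekly educational sessions". A 10-month phase of biweekly meetings follows.
- **Where attendance appears** (Mediator and Moderator Analyses). "Subgroup analyses will be conducted with respect to the number of sessions attended", alongside child sex, living standard and caregiver cognitive abilities. It is not part of the per-protocol definition.
- **Waitlist arm** (WLC Group). It receives the service only after the last assessment, so it has no facilitator during the trial.

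**The concern.** The purpose is a question about participants: did they receive enough of the programme for it to work? The membership rule is a statement about facilitators: did they deliver the sessions well? A set selected on the second does not answer the first.

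What is at stake is how a null or weak result is interpreted. If the per-protocol estimate is also null, the stated purpose invites the reader to rule out incomplete exposure and to blame the programme. That inference would not be justified, because dyads with little exposure have not been removed. If instead the per-protocol estimate is larger than the intention-to-treat estimate, the stated purpose invites an explanation in terms of exposure, when the selection was on delivery.

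**Working it through.** No figure in the plan depends on this point, so there is none to reproduce. The check sets the rule against its purpose and then shows the consequence in simple algebra.

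**Step 1: who is in the set.** Apply the rule to two caregivers in the DBS arm.

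| Caregiver | Sessions attended | Facilitator's two averages | In the per-protocol set? |
|---|---|---|---|
| A | few of 8 | both at or above 75% | yes |
| B | 8 of 8 | one below 75% | no |

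A is under-exposed and kept; B is fully exposed and dropped. Within the dyads of any one facilitator, the rule makes no distinction by attendance.

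**Step 2: what the set estimates, DBS versus waitlist.** Let *p* be the share of caregivers who attended adequately and *d* the effect in them, with no effect in the rest (an assumption). Use subscript H for dyads of facilitators who pass the fidelity rule and L for those of facilitators who fail. Let *w* be the share of dyads under passing facilitators.

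- Per-protocol effect = *p*_H × *d*_H
- Intention-to-treat effect = *w* × *p*_H × *d*_H + (1 − *w*) × *p*_L × *d*_L
- Difference = (1 − *w*) × (*p*_H × *d*_H − *p*_L × *d*_L)

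A null per-protocol effect can come from *p*_H near 0 (incomplete exposure) or *d*_H near 0 (deficient intervention). These are the two explanations that the analysis is meant to separate, and the estimate sees only their product. The difference from intention-to-treat also mixes attendance and effect.

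**Step 3: size in the simplest case.** Inputs: *d* = 0.5 SD, borrowed as a scale from the effect size in the Statistical Power section. The share of low attenders, *q* = 1 − *p*, is not given in the article, so a range is shown. Assume that attendance is unrelated to facilitator fidelity (*p*_H = *p*_L) and that the effect in attenders does not depend on it (*d*_H = *d*_L). Both analyses then give 0.5 × (1 − *q*).

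| Low attenders *q* (assumed) | Intention-to-treat | Per-protocol as defined | Effect in those exposed |
|---|---|---|---|
| 20% | 0.5 × 0.8 = 0.40 SD | 0.40 SD | 0.50 SD |
| 40% | 0.5 × 0.6 = 0.30 SD | 0.30 SD | 0.50 SD |
| 60% | 0.5 × 0.4 = 0.20 SD | 0.20 SD | 0.50 SD |

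Under these assumptions the per-protocol set recovers none of the dilution.

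**Step 4: the waitlist arm.** Membership requires having been taught by a qualifying facilitator. Waitlist dyads have none. Read literally, the rule admits no waitlist dyad, and the DBS-versus-waitlist comparison could not be made. If all are meant to be kept, exclusions fall only on the two active arms. The article does not say which is intended.

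**The case against.** **Attendance is analysed elsewhere.** The subgroup analysis by number of sessions attended does address exposure, and diaries and interviews monitored book-sharing at home. A reader would therefore not rely on the per-protocol result alone, and it would go too far to say that a null per-protocol result must be read as a failed programme. But the subgroup analysis is a separate one, on a variable that arises after randomisation and that the waitlist arm does not have. It is not the analysis given this purpose, and it does not remove the mismatch.

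**The details may be in a fuller plan.** An attendance threshold could be left to a document not shown. Here, however, the article states both a definition and a purpose, and they do not fit. That is different from silence.

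**The checklist includes caregiver behaviour.** This stands in part: attendance may be correlated with the facilitator score. A mean over 2 sessions per facilitator still cannot identify an under-exposed dyad, and a correlation would blend the two explanations rather than separate them.

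**Stronger readings that the text does not support.**
- The word *solely* might be taken to say that the set rests on fidelity alone. It limits the use of the scores; the evidence for the definition is the bracket after it.
- One might infer that a caregiver who attended nothing stays in. She was arguably not taught by anyone, so the example holds only for those who attended few sessions.
- One might infer that all waitlist dyads stay and that village balance is broken. The article states neither how waitlist dyads enter nor how facilitators map to villages, so imbalance is a possibility only.

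**Conclusion.** The point holds. The per-protocol rule as stated selects on delivery quality at facilitator level, while its stated purpose is to judge participants' exposure. It cannot separate a deficient intervention from incomplete exposure, and it leaves the waitlist arm unclassified.

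The mismatch itself needs no assumption; it follows from comparing the two sections. The claim that the set carries the same dilution as intention-to-treat does need assumptions: no gain in low attenders, and both attendance and the effect in attenders unrelated to facilitator fidelity. The SD values are illustrations over an assumed range of attendance, not predictions.

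The importance is moderate. Intention-to-treat is primary and no primary conclusion rests on this set. The plan should still be corrected, because the analysis is there to explain a null result and would mislead in that role.

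**What to change.** Reconcile Fidelity Testing with the Statistical Analysis Plan section before results are interpreted. The Results section says that data collection is complete and analysis is under way, so the change should be dated and made without reference to outcomes by attendance.

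1. Define the exposure analysis on the participant, with a pre-stated number of sessions attended, and say how waitlist dyads enter.
2. For DBS versus waitlist, preferably use a method that keeps all randomised dyads. A complier average causal effect is one option. Its assumptions should be stated, in particular that assignment acts only through attendance as defined. For DBS versus PA, where both arms have attenders, that method does not carry over simply and the approach needs its own wording.
3. Keep the ≥75% facilitator rule as a separate sensitivity analysis of delivery quality, adjusted for village and child age band, the factors considered in the randomisation.
4. If no participant-level criterion is added, restate the purpose of the per-protocol analysis as a check on delivery fidelity, and draw no conclusion about exposure from it.

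The cost is plan wording and one added secondary analysis with its assumptions. The planned analysis by sessions attended implies that the attendance data exist, so no new data should be needed. The alternative in item 4 costs wording only.

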### Data Management

Data were collected on tablets and mobile phones using a Kobo platform [51] and uploaded to a secure online server. Child assessments and caregiver-child book-sharing interactions were video recorded. A random sample of videos was regularly checked for fidelity of the data collection procedure. Interviews and focus groups were recorded on a voice recorder and checked for quality and adherence to the prescribed questions.

### Data Analysis

#### Statistical Analysis Plan

All data will be analyzed by an independent statistician using R (R Foundation for Statistical Computing) or Stata (StataCorp LLC). Fidelity will first be described with standard descriptive statistics. Hypothesis tests will be 2-sided with α of .05, and effect-size statistics will be reported to indicate the magnitude of any intervention effects.

Outcomes are classified a priori as primary, secondary, or exploratory. For the primary outcomes, we will use the Holm-Bonferroni method to adjust *P* values. Secondary and exploratory outcomes will be interpreted as hypothesis generating; the Benjamini-Hochberg procedure will be applied for their significance evaluation.

The primary and secondary outcome analyses will follow the intention-to-treat principle.

Linear mixed models or, where appropriate, analyses of covariance will evaluate intervention effects at both the intensive and extensive postintervention phases, always adjusting for baseline outcome scores. Because participants are clustered, a random effect will be included, and fixed-effect estimates will be compared with intercluster variability. Before modeling, every numerical predictor will be mean centered and standardized (*z* scores); interaction terms will be created as products of these centered variables. Candidate covariates and moderators (child age, dwelling place, child sex, socioeconomic situation, and parental cognitive abilities as indexed by education) will be retained only if they are significant or if removing them markedly alters other parameter estimates.

Although the intention-to-treat approach is the primary approach, a complementary per-protocol analysis will be performed to clarify whether any lack of impact arises from deficiencies in the intervention itself or from participants’ incomplete exposure to it.

Multicollinearity among predictors will be assessed using variance inflation factors, with appropriate mitigation strategies applied where necessary.

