### Aims

The aim of the EDBiT study is to assess the effects of DBS, a parenting program for female caregivers of children aged between 15 and 45 months, implemented in rural Tanzania. We aim to assess the impact of the intervention on the following domains: child cognitive and socioemotional skills, parenting and parental stress, and child health. We will evaluate the moderating influence of certain variables, including caregivers’ cognitive abilities.

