	**Moderators and selected confounding variables**																			
		Sex of the child	✓																	
		Socioeconomic situation	✓																	
		Cognitive abilities of the caregiver				✓														

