**Moderators and selected confounding variables**			
	Sex of the child	Child's sex (male or female)	
	Socioeconomic situation of families	Asset index	
	Parental cognitive abilities	Vienna Matrices Test	

^a^TOPSE: Tool to Measure Parenting Self-Efficacy.

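### Caregiver cognitive ability is defined as a Vienna Matrices score in the measures sections but as education in the analysis plan, so the variable for a moderator named in the Aims is not fixed

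*Protocol article*

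**What the plan says.** The Aims single out this moderator: "We will evaluate the moderating influence of certain variables, including caregivers’ cognitive abilities". Under Potential Moderators, the section on cognitive abilities of caregivers names the instrument: "The shortened version of the Vienna Matrices Test [50] was administered to measure the cognitive abilities of caregivers". Table 4 gives the same measure, "Vienna Matrices Test", against parental cognitive abilities. Table 3 schedules "Cognitive abilities of the caregiver" once, in the baseline column.

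The Statistical Analysis Plan section lists the model terms as follows: "Candidate covariates and moderators (child age, dwelling place, child sex, socioeconomic situation, and parental cognitive abilities", and completes the last item as "parental cognitive abilities as indexed by education". Terms on this list stay in the model only if they are significant or if dropping them markedly shifts other estimates.

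The Mediator and Moderator Analyses section plans interaction tests with possible moderators, and subgroup analyses by "the number of sessions attended, child sex, living standard, and the cognitive abilities of the caregiver". It does not say how cognitive ability is measured there.

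**The concern.** A matrices score and a record of schooling are different variables, and the article uses one name for both. An interaction with education answers whether the intervention works differently for caregivers with more or less schooling. An interaction with the test score answers whether it works differently by tested ability. Under a shared label, a null result for education could be read as no moderation by cognitive ability, and a positive one as evidence for it.

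The reading of this result matters to the sponsor. The Future Directions section raises the possibility of tailoring the programme for mothers with lower cognitive ability, and names mothers in extreme poverty as another group.

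Timing adds to the concern. The Results section says that data collection ended in September 2024 and that analysis is in progress. If the variable is not fixed in writing, it can be chosen after both versions have been looked at.

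**Working it through.** The plan gives no figure on this point, so there is nothing to reproduce. The check is a comparison of every place where the construct appears.

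| Place in the protocol article | Role | Measure named |
|---|---|---|
| Aims | moderator to be evaluated | none |
| Table 3 | moderator or confounder, assessed once at baseline | none |
| Table 4 | moderator or confounder | Vienna Matrices Test |
| Cognitive Abilities of Caregivers | potential moderator | Vienna Matrices Test, shortened |
| Statistical Analysis Plan | candidate covariate and moderator | education |
| Mediator and Moderator Analyses | moderator and subgroup variable | none |

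1. Two places name the test, one names education, and three name no measure. Table 4 and the moderator section agree with each other; the analysis plan agrees with neither.

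2. The conflict is not limited to covariate adjustment. The list that contains "parental cognitive abilities as indexed by education" is introduced as one of covariates and moderators alike, so it reaches the interaction terms too.

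3. No other text reconciles the two. Education is not an entry in Table 3 or Table 4 and is not described under Potential Moderators. The socioeconomic moderator is an asset index, and its description does not mention schooling. No sentence says that education replaces the test or why.

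4. The moderator section leaves both variables possible. A reader who follows the Potential Moderators section would use the Vienna score in the interaction. A reader who follows the Statistical Analysis Plan section would use education. Neither reading can be excluded from the text.

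5. The candidate covariate list has a retention rule that already depends on the data. An undecided definition of one of its members adds a second choice of that kind.

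**The case against.** The strongest reply is that the moderator analysis is specified in its own section, which names no measure, and that the only section defining this moderator names the Vienna test. On that view the education phrase belongs to the covariate list, and the Vienna score would still be used for moderation. This stands in part. A reader might infer that the plan discards the test score altogether; the documents do not establish that. But the list is explicitly one of moderators as well, so the reply shows that the text is ambiguous and does not show that it is settled.

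A second reply is that the absence of education from Tables 3 and 4 proves little, because both tables head that block as selected confounders and the article is condensed. That is fair: education may well have been recorded. The point here is the conflict between two stated measures, which does not depend on whether it was.

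A third reply concerns size. A reader might want to express the loss as shrinkage of the interaction in proportion to the correlation between education and tested ability, and from that derive a larger required sample. The documents give no such correlation. The calculation would also assume that education acts only as a proxy for ability and that the shortened test measures ability without error. No figure for lost power is supported. Nor do the documents show that education is closely tied to the asset index, so it cannot be said that an education interaction would in fact be an economic effect.

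**Conclusion.** The inconsistency is real, and nothing in the article resolves it. Following the Statistical Analysis Plan section literally would answer a stated aim with a variable whose measurement the article does not describe, under the name of one it does describe. Read with the moderator section, the choice remains open at a stage when the data are in hand.

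The effect is limited to one moderator and subgroup analysis and one candidate covariate. Outcome definitions, randomisation and the sample size calculation are untouched. A reader might infer that the main results are at risk; in a randomised comparison that always adjusts for the baseline outcome, exchanging one further baseline covariate should change the treatment estimate little. That last judgement rests on the usual behaviour of covariate adjustment under randomisation, not on a calculation from this trial. The point should be corrected, but it does not threaten the primary comparison.

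**What to change.** In the Statistical Analysis Plan section, replace the education phrase with the baseline Vienna Matrices score. It can be standardised under the rule the plan already sets for numerical predictors. In the Mediator and Moderator Analyses section, name the same score for both the interaction test and the subgroup analysis.

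If education was recorded and is wanted, list it separately under its own name, either as a covariate or as a labelled sensitivity analysis, and state where the data come from.

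If the sponsor did intend education, for instance because the test performed poorly in this population, state the reason, amend Table 4 and the section on caregivers' cognitive abilities to match, and report the result as moderation by education.

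In either case, date the decision before the moderator models are run; if any have already been run, say so. The cost is a few words. No new data are needed for the first option, since the article reports that the test was administered.
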